**Methods/design:**

Multicentre, single-blinded, randomized controlled trial comparing standard preoperative work-up to a preoperative work-up with addition of the prediction model. Tumour volume to breast volume ratio and tumour location in the breast will be used to predict cosmetic outcome in invasive breast cancer patients opting for BCS. Three dimensional (3D)-ultrasonography will be used to measure the tumour volume to breast volume ratio needed for the prediction model. Sample size was estimated based on a 14% improvement in incidence of superior cosmetic result one year after BCS (71% in the control group versus 85% in the intervention group). Primarily cosmetic outcome will be evaluated by a 6-member independent panel. Secondary endpoints include; (1) patient reported outcome measured by BREAST-Q, EORTC-QLQ-C30/BR23 and EQ-5D-5 L (2) cosmetic outcome as assessed through the BCCT.core software, (3) radiation-induced reaction (4) surgical treatment performed, (5) pathological result and (6) cost-effectiveness. Follow-up data will be collected for 3 years after surgery or finishing radiotherapy.

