### Interventions

#### Volumetric measurements

All patients will receive an additional ultrasound performed by the Automated Breast Volume Scanner (ABVS– ACUSON S2000™ ABVS, Siemens Medical Solutions, Inc., Mountain View, CA) available at the department of Radiology, Erasmus MC Cancer Institute [14]. A standardized scanning technique is used where 3 or 5 scans are performed (i.e. anterior-posterior, lateral and medial view or anterior-posterior, upper lateral-, lower lateral-, upper medial- and lower medial-quadrant). Data from the ABVS is visualised by the ‘V-scope’ software (department of Bioinformatics, Erasmus MC) through an interactive 3-D image on the desktop system. Volume measurements are performed using a tracking system and a wireless joystick [15].

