#### Prediction model

The tumour to breast volume ratio and the location of the tumour in the breast are used in the prediction model to calculate the chance of superior cosmesis in case of BCS. If the probability exceeds the predefined threshold primary BCS is advised. If the probability is below the predefined threshold an alternative treatment will be advised (i.e. oncoplastic BCS, mastectomy with or without a breast reconstruction or neo-adjuvant chemotherapy). The threshold is defined by modelling the differences in quality of life utilities between the different surgical strategies and the associated cosmetic results.

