#### Pre-operative work-up

For all randomized patients the following characteristics will be collected (if applicable): age, body mass index (BMI), comorbidity, previous operations, smoking status, hormonal status, tumour morphology, TNM stadium, post-operative complications, radiotherapy details, chemotherapy details and hormonal therapy details.

Preoperatively all patients will be asked to complete three questionnaires. This includes the ‘Breast Q – preoperative modules’ [16], the ‘European Organisation of research and Treatment of Cancer quality of life questionnaire (EORTC-QLQ-C30 version 3 and EORTC-QLQ-B23 version 1)’ and ‘Euro-QoL 5D-5 L questionnaire’ (EQ-5D-5 L-version 2). All patients will preoperatively be discussed in multidisciplinary consultation. For the intervention group, the optimal treatment based on the results of the prediction model will be taken into consideration. All patients will be blinded for the result of the prediction model. Preoperative photographs will be taken by a professional medical photographer. These photographs include the 1) face-view position with the arms down, 2) face-view with arms in the side and 3) lateral view (90°) off the affected breast. The face view photographs will cover the area of chin to the umbilicus protecting the subject’s privacy and anonymity.

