#### Secondary study parameters

Cosmetic result assessed by the patient (BREAST-Q), cosmetic evaluation through BCCT.core and radiation-induced reaction (RTOG/EORTC) will be analysed by comparing the intervention and control group. For normally distributed categorical data, the Chi-Square test will be used and the Kruskal Wallis test if not normally distributed. Continues variables as the Q-score will be analysed making use of the Student T-test if normally distributed or Mann-Whitney U test if not normally distributed. Pathological result will be analysed by comparing the percentages of incomplete tumour excisions and mean lumpectomy specimen size between the two study arms. The secondary study parameters will be analysed based on the intention-to-treat principle (i.e. including the patients treated with mastectomy). Surgical strategies performed will be analysed by comparing the percentages of the different types of surgery performed by using a Chi-square analysis if normally distributed or Kruskal-Wallis test if not normally distributed. Patients’ quality of life, conducted through the EORTC questionnaire/Euro-QoL and BREAST-Q questionnaires will be presented in a quantitative manner. Cost-effectiveness will be calculated by Markov modelling using ‘Quality-Adjusted Life Years’ (QALY’s).

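### The raw comparison of mean lumpectomy specimen size mixes tissue removed for a given tumour with which tumours reach lumpectomy; adjust for the tumour and breast volumes measured before surgery

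*Protocol article*

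**What the plan says.** All places are in the protocol article.

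- **Secondary study parameters.** Pathological result is analysed through the percentage of incomplete excisions and "mean lumpectomy specimen size between the two study arms". Continuous variables are tested "making use of the Student T-test if normally distributed or Mann-Whitney U test if not normally distributed". The secondary parameters follow intention-to-treat, "including the patients treated with mastectomy".
- **Volumetric measurements.** "All patients will receive an additional ultrasound performed by the Automated Breast Volume Scanner". The abstract says that 3-D ultrasonography "will be used to measure the tumour volume to breast volume ratio needed for the prediction model". Nothing restricts the volume measurement to one arm.
- **Prediction model.** The inputs are the volume ratio and the tumour location. "If the probability is below the predefined threshold an alternative treatment will be advised", the options being "oncoplastic BCS, mastectomy with or without a breast reconstruction or neo-adjuvant chemotherapy".
- **Pre-operative work-up.** "For the intervention group, the optimal treatment based on the results of the prediction model will be taken into consideration". Nothing similar is planned for the control arm.
- **Sample size.** Mastectomy after randomisation is expected in fewer than 25% of each arm; 150 patients per arm are planned.

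No section relates specimen size to tumour or breast volume, or says how patients without a lumpectomy specimen enter the comparison.

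**The concern.** A lumpectomy specimen exists only for patients who have a lumpectomy, and that is settled after randomisation. In the intervention arm the decision can follow the volume ratio and location through the model's advice; in the control arm it follows usual judgement. If the advice is acted on, the intervention lumpectomies can contain fewer tumours that are large for the breast. Randomisation then no longer balances tumour size among the patients compared, and mean specimen size can differ even if surgeons remove exactly the same tissue around a given tumour.

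At stake is the interpretation of one pathology endpoint. A difference could be taken as a change in how much is excised when it reflects a change in which tumours were excised. An opposite shift could hide a real change. The unadjusted mean also carries all the between-patient variation in tumour size, which costs precision.

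**Working it through.** The article gives no mean, SD or expected difference for specimen size, so there is no stated figure to reproduce. The check asks what the raw comparison shows when resection for a given tumour is identical in both arms.

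**Assumed inputs (none from the article except 150 per arm).** Log tumour volume T has SD 0.9 and log breast volume B has SD 0.45, independent. Log specimen = k·T + 0.2·B + noise with SD 0.4, and k = 0.3 to 0.5. Log ratio = T − B.

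**One case by hand.** The intervention arm loses the 20% with the highest ratio; control loses none.

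- SD of log ratio = √(0.81 + 0.2025) = 1.006.
- Mean of the lower 80% of a standard normal = −0.280/0.8 = −0.350.
- Shift in T = (0.81/1.006) × (−0.350) = −0.282. Shift in B = (0.2025/1.006) × 0.350 = +0.070.
- Shift in log specimen, k = 0.3: 0.3 × (−0.282) + 0.2 × 0.070 = −0.070, a geometric mean 6.8% lower. For k = 0.5: −0.127, or 11.9% lower.
- Test at k = 0.3: SD = √(0.0729 + 0.0081 + 0.16) = 0.491. SE = 0.491 × √(1/150 + 1/120) = 0.060. z = 1.17, so a two-sided 5% test rejects in about 22% of trials.

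**Range by simulation of the same model (k = 0.3 to 0.5; raw arithmetic means, test on log size).**

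| Who does not reach lumpectomy | Raw mean, intervention vs control | Rejections at 5% |
|---|---|---|
| Intervention: top 15–25% by ratio. Control: 0–10%, weakly related to ratio | 5–17% lower | 12–55% |
| 20% in each arm; selection correlates 0.8 with ratio in intervention, 0.3 in control | 4–8% lower | 9–13% |
| Intervention: top 20% by ratio. Control: 20%, correlation 0.8 | 2–4% lower | about 6% |
| Both arms select on the ratio equally strongly | about 0 | about 5% |
| Intervention flags top 20%, control loses 5%; half of those flagged have oncoplastic surgery with unchanged specimen size | 3–5% lower | 7–10% |
| As above, with the advice followed in half | 1–2% lower | 5–6% |

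If oncoplastic specimens are 1.5 times larger (an assumption), the sign reverses, to between 2% and 10% higher depending on the loss pattern.

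**A different specimen model.** Take specimen volume = (30 + b × tumour volume) mL with b = 3 or 6. The intervention arm diverts the top 10–25% of ratios with 50–100% adherence, and control diverts 0–25% regardless of ratio. The raw mean is 3–18% lower, with 8–75% rejections.

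**After adjustment.** With the relevant volumes as covariates, the arm effect returns to about zero in both models when there is no true difference. By 1 − √(1 − r²), a correlation of 0.55 to 0.74 between log specimen and log tumour volume would also cut the standard error by about 16–33%, somewhat less once selection has narrowed the range of tumour sizes.

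**Why not divide by tumour volume.** Specimen/tumour varies as tumour volume to the power k − 1, that is −0.7 to −0.5, so it rises as tumours get smaller. In the hand case its log shift is −0.070 + 0.282 = +0.212 at k = 0.3 (about 24% higher) and −0.127 + 0.282 = +0.155 at k = 0.5 (17% higher). Across the loss patterns tried it is 10–30% higher in the intervention arm with no true effect, and rejects in 27–83% of trials, more often than the raw mean.

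**The case against.** Four counter-arguments deserve weight.

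1. *The article makes no per-tumour claim.* Nowhere does it say that a smaller mean would show less tissue removed per tumour, and a change in which tumours reach lumpectomy is part of what the strategy does. This stands: a reader might infer that the plan asserts smaller excisions, and the text does not support that. But the raw mean is not a clean strategy comparison either, since patients without a lumpectomy specimen drop out of it despite the intention-to-treat statement.

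2. *Size and direction are uncertain.* A reader might infer that the intervention mean will be spuriously smaller by a predictable amount. The documents do not support this. The advice is only weighed in the multidisciplinary discussion, and oncoplastic surgery and neo-adjuvant chemotherapy can still end in a breast-conserving specimen. One mastectomy bound is given for both arms, and control surgeons may already select on the ratio. This stands in full; what survives is that the raw difference cannot be read either way.

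3. *The adjusted zero holds by construction.* In the simulations selection runs only through the covariates, and the fitted form is the generating form. This also stands. Adjustment removes selection that acts through volume and location, not all selection, and does not turn the lumpectomy subset back into a randomised comparison.

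4. *Adjustment belongs in an analysis plan that is not shown.* That is partly right, and it keeps the point small. However, the article does name the statistic and only unadjusted tests, so a change there is appropriate.

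**Conclusion.** The point holds as a minor one. The article fixes an unadjusted comparison in a subset whose make-up can depend on arm through tumour-to-breast ratio and location, so a raw difference cannot separate case mix from tissue removed for a given tumour. Under the first specimen model, the artefact runs from about zero with equally strong selection in both arms to about 17% lower in the intervention arm, and larger oncoplastic specimens could make it positive. Equal numbers lost per arm do not remove it; equal selection on the ratio does. All these figures rest on assumed volume distributions, adherence and control practice. The mechanism itself rests only on the article's text. The primary outcome and the sample size are not affected.

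**What to change.** In Secondary study parameters, replace the raw comparison by a linear model for log specimen size among patients with a lumpectomy. Include arm, log preoperative tumour volume, log breast volume and tumour location, with the volumes taken from the scan that every patient has. Report the adjusted ratio of specimen size with its 95% CI. In addition:

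- keep the raw mean per arm as description;
- give the number without a lumpectomy specimen per arm, and state whether oncoplastic specimens count;
- label the result as conditional on lumpectomy, not a full intention-to-treat contrast;
- do not use the specimen-to-tumour volume ratio;
- add a sensitivity analysis without patients who had neo-adjuvant treatment, because their covariate is the volume before treatment.

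The cost is a change to the analysis text, with no new patients or measurements if volumes are read from every scan. The downside is small: the estimate is a conditional, adjusted ratio, less immediate than a difference in means.

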#### Follow-up

Three questionnaires will be obtained at all follow-up visits (i.e. ‘BREAST-Q postoperative modules’, the EORTC-QLQ-C30/B23 and the EQ-5D-5 L. Follow-up visits will be scheduled at 3 months (T1), 1 year (T2), and 3 year (T3) postoperatively. Photographs will be obtained both 1 and 3 year following BCS.

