### Sample size

In our previously performed retrospective study the incidence of a superior cosmetic result, without intervention, was 71%. An improvement of superior cosmetic outcome to 85% was considered clinically relevant. Expected clinical relevant difference is a 14% improvement in the incidence of a superior cosmetic result as evaluated by an independent panel. The sample size calculation is based on comparing two proportions in independent groups by the Chi-Square test. With 80% power and 5% significance level we need a study population of 240 patients (120 in each arm). There is a possibility that even after randomization the patient can still undergo mastectomy instead of BCS. We expect this for less than 25% patients in each arm, therefore we aim to include 300 patients in total (150 in each arm).

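### The plan implies that the primary cosmetic comparison counts only patients who had breast-conserving surgery, a group that the intervention's own advice can alter

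*Protocol article*

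**What the plan says.** The Primary study parameter section defines the outcome as the proportion with a superior panel score in each arm. It does not say which patients enter the comparison. Four other places bear on that:

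- **Abstract, Methods/design:** the planned 14-point gain is described as a result one year after BCS.
- **Follow-up:** "Photographs will be obtained both 1 and 3 year following BCS". The panel scores these photographs, so they are the source of the primary outcome.
- **Sample size:** "There is a possibility that even after randomization the patient can still undergo mastectomy instead of BCS". This is expected in under 25% of each arm and is the stated reason for raising 240 patients to 300.
- **Secondary study parameters:** "The secondary study parameters will be analysed based on the intention-to-treat principle (i.e. including the patients treated with mastectomy". No such sentence covers the primary outcome.

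On the intervention, the Prediction model section says: "If the probability is below the predefined threshold an alternative treatment will be advised". The alternatives listed are oncoplastic BCS, mastectomy with or without reconstruction, and neo-adjuvant chemotherapy. The Pre-operative work-up section says that the model's result is considered in the multidisciplinary consultation for the intervention group only.

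**The concern.** Raising the total to allow for mastectomy makes sense only if mastectomy patients do not count towards the 240. If photographs are taken only after BCS, those patients also have no primary outcome data.

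Whether an intervention patient is excluded would then depend on the allocated arm and on the predicted value of the primary outcome. Patients with a poor predicted result can leave the intervention denominator, while similar patients stay in the control denominator. The superior rate among the remaining intervention patients rises although nobody's breast looks better. The comparison is no longer protected by randomisation, yet the Discussion section presents the trial as a source of level 1B evidence.

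This goes beyond a detail that a statistical analysis plan can settle later, because photographs that were never taken cannot be recovered.

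**Working it through.** **1. The plan's own figures.** The inputs in the Sample size section are a control rate ("the incidence of a superior cosmetic result, without intervention, was 71" per cent), a target ("An improvement of superior cosmetic outcome to 85% was considered clinically relevant") and a base size ("With 80% power and 5% significance level we need a study population of 240 patients (120 in each arm").

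- The step to 300 can be reproduced as 240 × 1.25 = 300, or as 240 / (1 − 0.20) = 300. A full 25% loss would need 240 / 0.75 = 320. Each version treats mastectomy patients as lost to the primary analysis.
- As a separate matter, a two-sided chi-square test of 71% vs 85% needs 137 per arm for 80% power, and 120 per arm gives about 75%. The point here does not depend on this.

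**2. Model for the selection effect.** Suppose that no patient's BCS result changes and that the only effect of the advice is to move some patients to mastectomy.

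- f = share of patients below the threshold; assumed 25%
- s = superior rate of those patients if they had BCS; assumed 30-50%
- a = share of those patients moved to mastectomy in the intervention arm; varied
- overall superior rate under BCS = 71% (Sample size section)
- control arm: all 150 have BCS (assumed)

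BCS-only rate in the intervention arm = (0.71 − f·a·s) / (1 − f·a), with 150 × (1 − f·a) patients. The documents give neither f, s nor a. Their only constraint is mastectomy below 25%, so the row with a = 100% sits at that ceiling.

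**3. Results.** The last column is the exact probability that an uncorrected chi-square test is significant at 5% in favour of the intervention (nominal 2.5%).

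| a | s | Calculation | Intervention rate | Difference from 71% | Patients, control / intervention | Significant in favour |
|---|---|---|---|---|---|---|
| 20% | 50% | 0.685 / 0.95 | 72.1% | +1.1 | 150 / 142 | 4% |
| 40% | 30% | 0.680 / 0.90 | 75.6% | +4.6 | 150 / 135 | 14% |
| 60% | 50% | 0.635 / 0.85 | 74.7% | +3.7 | 150 / 128 | 10% |
| 80% | 40% | 0.630 / 0.80 | 78.75% | +7.75 | 150 / 120 | 31% |
| 100% | 30% | 0.635 / 0.75 | 84.7% | +13.7 | 150 / 112 | 75% |

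**4. Two checks on the mechanism.**

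- If the patients moved are like everyone else (s = 71%), the rate is 0.71 × (1 − f·a) / (1 − f·a) = 71%, and there is no bias.
- Equal numbers excluded do not remove the bias. In the 80% / 40% row, if 20% of control patients also have mastectomy for reasons unrelated to expected cosmesis (120 vs 120 analysed), the chance is still about 28%.

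**5. Mastectomy counted as not superior.** In the same 80% / 40% row, the intervention rate becomes 0.71 − 0.25 × 0.80 × 0.40 = 63% against 71%. The chance of a significant result against the intervention is then about 31%, so the sign depends on the population chosen. This rule also costs power when 71% vs 85% holds among BCS patients and mastectomy is equally common in both arms:

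- 20% mastectomy: 71% × 0.80 = 56.8% vs 85% × 0.80 = 68.0%; power at 150 per arm about 52%.
- 25% mastectomy: 53.25% vs 63.75%; power about 47%.

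**The case against.** **The population is inferred.** A reader might conclude that the protocol states a BCS-only primary analysis. It does not. The section that defines the primary outcome is silent, the Sample size section never says that mastectomy patients are excluded, and Table 2 times the assessments from surgery in general. The article is also condensed. This limits the claim to an implication, but four places point the same way and none points the other way.

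**The advice does not decide who has BCS.** A reader might infer that the model determines the operation. It is one input to a consultation. Oncoplastic BCS and neo-adjuvant chemotherapy can both end in BCS, so those patients can stay in the analysis, and any real gain for them is what the trial is meant to detect. This stands. It is why low uptake of mastectomy (20-40%) belongs in the range, and there the bias is modest.

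**The direction is conditional.** The bias needs a model that discriminates. It also shrinks to the extent that surgeons in the control arm already move similar patients to mastectomy. Both points stand. The trial's rationale, however, assumes that the model discriminates and adds something to usual judgement.

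**A simple remedy can do its own harm.** Counting every mastectomy as a failure looks like strict intention-to-treat. It would score patients who followed the model's advice as failures, including those reconstructed, and it reverses the bias instead of removing it. This stands and shapes the fix.

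**Conclusion.** The concern holds in this form. The primary population is unstated, the rest of the article implies BCS-only, and that population can be changed by the intervention on the basis of the predicted primary outcome. If the model discriminates, the comparison leans towards the intervention with no patient improved.

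The size cannot be fixed from the documents. Under the stated assumptions it runs from about 1 point and a 4% chance of a false positive to nearly the whole planned 14 points and 75%. No single row is the expected bias, and the upper end requires every below-threshold patient to have mastectomy. The documents do not support saying that the trial will give a false-positive result. They do show that the design lacks protection against one.

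A smaller point: the intention-to-treat rule for secondary outcomes cannot include mastectomy patients for lumpectomy specimen size, and does not plainly apply to BCCT.core, a breast-conservation tool.

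**What to change.** 1. In Primary study parameter, state that the primary outcome is analysed by intention-to-treat in all randomised patients, by allocated arm, at one year.
2. In Follow-up, have the one-year photographs taken at the existing visit after any surgery, and have the independent panel score them wherever its questionnaire can be applied.
3. Label the BCS-only comparison as supportive and non-randomised.
4. Do not make mastectomy equal to not superior the primary rule. Report it only as a sensitivity bound beside the BCS-only result, because the two can differ in sign.
5. In Sample size, state that 71% and 85% apply to all randomised patients. If they do, 150 per arm gives about 84% power.
6. In Secondary study parameters, label lumpectomy specimen size and BCCT.core as BCS-only and descriptive.

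**Cost:** wording changes, plus one-year photographs for the mastectomy patients (under 25% of 300, so fewer than 75). The superior rate may look less favourable. It must also be confirmed, before outcome data are seen, that the panel questionnaire can score a mastectomy or a reconstruction; it is in an additional file that is not shown.

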#### Primary outcome

The cosmetic outcome evaluation will be performed by a 6-member, independent panel using the photographs. Each panel consist of 1) a plastic surgeon/breast cancer surgeon, 2) a general practitioner, a medical doctor, 3) a radiation oncologist, 4) a layperson and 5) a breast cancer survivor. Cosmetic outcome will be evaluated using a previously reported in-house developed questionnaire containing 11 aggregating previous recommendations [17] (see Additional file 1 A ‘Erasmus MC panels’ questionnaire’). Answers are scored on a four point Harvard cosmetic scale: 0 = ‘excellent’, 1 = ‘good’, 2 = ‘moderate’, and 3 = ‘bad’ [18].

*Secondary outcome(s).*

1) Patient reported outcome is measured by the ‘BREAST-Q’, ‘EORTC-QLQ-C30/BR23’ and ‘EQ-5D-5 L’ questionnaires (T0–3).

2) Cosmetic outcome assessed by the ‘BCCT.core software’ - INESC Porto Breast Research group [19] based on medical photographs (T0–2-3).

3) Radiation reaction scored by the ‘Radiation Therapy Oncology Group/European Organization for Research and Treatment of Cancer’ – ‘RTOG/EORTC’ (T2–3) [20].

4) Surgeries performed (T3).

5) Pathological results (T3).

6) Cost-effectiveness*;* direct costs will include the pre-operative care together with the costs for (surgical) treatment. Indirect costs will generally include adjuvant operation(s) if applicable and costs of outpatient clinic visits or hospitalisation (T4).

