Preoperative assessment of patients’ quality of life and satisfaction with their breast is currently lacking in the literature available. Only few trials have combined postoperative cosmetic outcome measurements by panel or software with patient reported outcome measures (PROMs) [21–23]. Especially an evaluation of cosmetic outcome through time following breast surgery is scarce [21]. By preoperatively collecting aesthetics and PROMs a reliable understanding of the relationship between cosmetic results and self-image or quality of life is gained. Comparing overall health-related quality of life (EORTC-QLQ-C30/B23 and EQ-5D-5 L) and treatment- or surgery specific outcomes (BREAST-Q) gives a better understanding between overall and disease-specific quality of life [16, 24, 25]. With this knowledge, future treatment decision making and cosmetic outcome evaluation can possibly be based on PROMs. To adequately study cosmetic outcome and their relationship to PROM’s, standardized, reproducible and easily available tools are needed [18, 26]. Comparing two different panel evaluations within 68 patients following BCS our group found almost perfect inter- and intra-observer agreement. Interclass correlation coefficient showed *R* = 0.93, *R* = 0.9 respectively for the inter- and intra-observer agreement [unpublished data]. When comparing trials differences in panel evaluations found are based on panel size and the use of layperson versus experts [23, 27, 28]. Moreover multiple and unstandardized questionnaires are used to obtain cosmetic outcome; making a comparison between different trials difficult. Based on previous recommendations of Cardoso et al. our current study uses a questionnaire concerning the different aspect of cosmetic outcome when evaluating the breast by panel members [17]. The BCCT.core software is known to evaluate asymmetry, skin colour difference(s) and scar features based on the situation of two identical breasts [29–31]. In line with previous literature our group found a moderate agreement (unpublished data) between panel and BCCT core evaluation [22, 23]. An independent 6-member panel will therefore assess cosmetic outcome as our primary outcome. In summary this study aims to improve cosmetic outcome and quality of life through the implementation of a preoperative prediction model for breast cancer patients opting for BCS.

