## Abbreviations

3-D: Three-dimensional
ABVS: Automated Breast Volume Scanner
BCS: Breast Conserving Surgery
BCCT.core: Breast Cancer Conservative Treatment. cosmetic result
BRA: Breast Retraction Assessment
DSMB: Data Safety Monitoring Board
EORTC-QLQ: European Organisation of Research and Treatment of Cancer quality of life questionnaire
EQ-5D-5 L: Euro-QoL-5D-5 L
QALY’s: Quality-Adjusted Life Years
RTOG/EORTC: Radiation Therapy Oncology Group/European Organization for Research and Treatment of Cancer
US: Ultrasonography

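### Intention-to-treat is promised for every secondary outcome, but lumpectomy specimen size, and largely BCCT.core, have no value after mastectomy

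*Protocol article*

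**What the plan says.** All references are to the Protocol article.

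- **Analysis set.** Secondary study parameters: "The secondary study parameters will be analysed based on the intention-to-treat principle (i.e. including the patients treated with mastectomy". No outcome is excepted.
- **Specimen size.** The sentence just before that one compares incomplete excisions and "mean lumpectomy specimen size between the two study arms".
- **BCCT.core.** The same section says that "cosmetic evaluation through BCCT.core and radiation-induced reaction (RTOG/EORTC) will be analysed by comparing the intervention and control group", with no subset named. The outcome list describes the score as "based on medical photographs (T0–2-3". The Follow-up section says: "Photographs will be obtained both 1 and 3 year following BCS". The Discussion says the software is known to "evaluate asymmetry, skin colour difference(s) and scar features based on the situation of two identical breasts", and the Abbreviations expand the name as "BCCT.core: Breast Cancer Conservative Treatment. cosmetic result".
- **Role of the model.** Under Prediction model, a patient below the threshold is advised an alternative: oncoplastic BCS, mastectomy with or without reconstruction, or neo-adjuvant chemotherapy. Under Pre-operative work-up, the model result is taken into account for the intervention group only.
- **Expected mastectomies.** Sample size expects mastectomy after randomisation in less than 25% of each arm, with 150 patients per arm.

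**The concern.** An intention-to-treat analysis that includes mastectomy patients needs an outcome value, or a rule that supplies one, for each of them. Lumpectomy specimen size has none by definition. BCCT.core has no planned follow-up image after mastectomy, and a breast removed without reconstruction does not meet the two-breast premise that the article gives for the software.

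In practice both outcomes will be analysed in the patients who had BCS. Whether a patient has BCS is settled after randomisation, and the intervention is designed to influence that decision. The results would carry an intention-to-treat label, and a reader would take them as randomised evidence. They would in fact compare two subsets that may differ in tumour-to-breast volume ratio and tumour location, the two factors on which the model acts.

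**Working it through.** **1. Which secondary outcomes are defined for every randomised patient?**

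| Outcome | Defined after mastectomy? | Basis in the article |
|---|---|---|
| BREAST-Q, EORTC, EQ-5D-5L | Yes, in principle | Questionnaires at all follow-up visits |
| Surgery performed | Yes | Any operation counts |
| Incomplete excision | Yes, in principle | Pathology reports |
| Costs | Yes | Treatment and care costs |
| Lumpectomy specimen size | No | Needs a lumpectomy |
| BCCT.core | Not as scheduled; open if reconstructed | Follow-up photographs tied to BCS; premise of two alike breasts |
| Radiation reaction | Not settled | Radiotherapy after mastectomy is not addressed |

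The conflict is therefore clear for specimen size, well supported for BCCT.core and not shown for the others.

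**2. How many patients?** Inputs from Sample size: 150 per arm; mastectomy below 25% in each arm.

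- Upper limit per arm: 0.25 × 150 = 37.5. Since the rate is below 25%, this is at most 37.
- Both arms: 2 × 37 = 74 of 300.
- Remaining per arm: 150 − 37 = 113.

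The article gives no rate by arm. If mastectomy in an arm is assumed to lie between 5% and 25%, the number with a value runs from 150 × 0.95 = 142.5 (about 142) down to about 113. At an assumed 10% it is 150 × 0.90 = 135.

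**3. Why is the remaining comparison not randomised?** What would be estimated is

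mean(Y | BCS, intervention) − mean(Y | BCS, control).

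Randomisation makes the two whole arms comparable. It makes the two BCS subsets comparable only if the type of operation does not depend on allocation in a way related to Y. Here such a dependence is intended, because the model result enters the decision in one arm only and selects on volume ratio and location. Equal mastectomy percentages would not cure this: the same number of patients could be removed from each arm with different characteristics.

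**4. Can the direction be derived?** No. A high ratio may reflect a large tumour or a small breast. Patients below the threshold may also be advised oncoplastic BCS or neo-adjuvant chemotherapy and so still contribute a specimen.

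**5. Can the proposed adjustment be computed?** Yes. Under Volumetric measurements all patients receive the additional scan, so the ratio, and with location the predicted probability, can be obtained in both arms.

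**The case against.** The strongest reply has three parts.

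*Intention-to-treat can mean simply comparing patients by allocated arm, and a lumpectomy outcome carries its own denominator.* This is partly right: nothing in the article prevents reporting evaluable numbers. But the article defines its use of the term as including mastectomy patients, directly after naming the specimen outcome, so the sentence would have to change.

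*The BCS wording for photographs may be loose.* Table 2 lists BCCT.core at T0, T2 and T3 without restriction, and some mastectomy patients may be reconstructed. This stands as a caveat, and it is why BCCT.core is called largely rather than wholly affected.

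*Analysis sets per outcome belong in an analysis plan that is not shown.* This would answer a complaint about missing detail. The point here is a stated rule that two of the outcomes cannot satisfy.

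Three stronger readings are tempting and are not supported:

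- A reader might add radiation reaction to the outcomes without a value. The article does not say that mastectomy patients go unirradiated, and recording no reaction in a patient never irradiated is a possible result of allocation. Restricting that outcome to irradiated patients is a debatable choice of estimand. Any calculated bias would need reaction rates and mastectomy rates by arm that the article does not give.
- A reader might infer that the mean specimen must shrink in the intervention arm. That is plausible, but it does not follow from the article (step 4 above).
- A reader might conclude that intention-to-treat fails for the secondary outcomes as a whole. It remains workable for most of them.

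**Conclusion.** The point holds for two secondary outcomes: fully for mean lumpectomy specimen size, and for BCCT.core subject to the open question of reconstruction. The number affected is bounded by the plan's own ceiling, at most 37 of 150 per arm. This assumes that the ceiling is met and that no mastectomy patient is photographed and scored. The size of any bias is unknown because mastectomy by arm is not stated. The primary outcome is not at issue here, and the matter is one of correct labelling and cheap bias reduction. It should still be corrected, because following the sentence as written would present subsets shaped by the intervention as a randomised comparison.

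**What to change.** - Limit the intention-to-treat sentence to outcomes defined for every randomised patient: BREAST-Q, EORTC, EQ-5D-5L, surgery performed, incomplete excision and costs.
- State that specimen size and BCCT.core are reported in patients treated with BCS, and give the number evaluable in each arm. If reconstructed patients are meant to have BCCT.core scores, say so and align the photograph schedule.
- Adjust both comparisons for the model's predicted probability and label them non-randomised. Adjustment should reduce the imbalance that the model creates, but it does not restore randomisation.

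The cost is a change of wording, with no new data unless reconstructed patients are to be photographed. The downside is that two secondary outcomes lose the intention-to-treat label.
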